# The (cost-)effectiveness of an implemented fall prevention intervention on falls and fall-related injuries among community-dwelling older adults with an increased risk of falls: protocol for the in balance randomized controlled trial

**DOI:** 10.1186/s12877-021-02334-3

**Published:** 2021-06-23

**Keywords:** Fall prevention, Effectiveness, Ageing, Elderly, Accidental falls, Intervention studies, Cost-effectiveness, Healthcare utilization

## Abstract

**Background:**

Falls and fall-related injuries among older adults are a serious threat to the quality of life and result in high healthcare and societal costs. Despite evidence that falls can be prevented by fall prevention programmes, practical barriers may challenge the implementation of these programmes. In this study, we will investigate the effectiveness and cost-effectiveness of In Balance, a fourteen-week, low-cost group fall prevention intervention, that is widely implemented in community-dwelling older adults with an increased fall risk in the Netherlands. Moreover, we will be the first to include cost-effectiveness for this intervention. Based on previous evidence of the In Balance intervention in pre-frail older adults, we expect this intervention to be (cost-)effective after implementation-related adjustments on the target population and duration of the intervention.

**Methods:**

This study is a single-blinded, multicenter randomized controlled trial. The target sample will consist of 256 community-dwelling non-frail and pre-frail adults of 65 years or older with an increased risk of falls. The intervention group receives the In Balance intervention as it is currently widely implemented in Dutch healthcare, which includes an educational component and physical exercises. The physical exercises are based on Tai Chi principles and focus on balance and strength. The control group receives general written physical activity recommendations. Primary outcomes are the number of falls and fall-related injuries over 12 months follow-up. Secondary outcomes consist of physical performance measures, physical activity, confidence, health status, quality of life, process evaluation and societal costs. Mixed model analyses will be conducted for both primary and secondary outcomes and will be stratified for non-frail and pre-frail adults.

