Considering the adjustments in both duration and target population of the original In Balance intervention, re-evaluation of the effectiveness of the intervention is urgently needed. Moreover, evidence on the cost-effectiveness of fall prevention programmes is scarce [26]. Cost-effectiveness analysis of the In Balance intervention would allow insurance companies, policy- and decision makers to allocate health resources efficiently. Therefore, this study aims to assess the effectiveness and cost-effectiveness from a societal perspective of the In Balance fall prevention intervention compared to written general physical activity recommendations on the number of falls with and without injuries for community-dwelling adults of 65 years or older with an increased fall risk, stratified for frailty status (non-frail and pre-frail).

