### Data collection and outcome measures

#### Primary outcome measure

The primary outcome in this study is the number of falls, with or without injuries, assessed with fall diaries and monthly follow-up telephone calls, including questions on the causes, circumstances and consequences of falls. This combination of pro- and retrospective data collection follows guidelines for conducting fall prevention trials [41].

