#### Secondary outcome measures

Besides the number of falls and fall-related injuries, positive effects on physical functioning, physical activity, quality of life and other self-reported outcome measures are measured [42]. The secondary outcome measures will be assessed at three time points during the study period; at entry of the study (baseline, M0), after 4 months to determine the short-term effects (M4) and after 12 months to determine the long-term effects (M12). Societal costs will be assessed at M4, after 8 months (M8) and M12. All secondary outcomes are listed in Table 2 and are described in detail below.

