### Sample size

To obtain a reduction of 50% in the number of falls between the intervention and control group, a minimum of 106 persons are required per group, at a power of 0.80, beta of 0.02 and alpha of 0.05. Taking into account a dropout rate of 20%, the total required sample size is 256 participants. Hence, we expect that about 16 In Balance intervention groups of 8 participants each, are needed to include the required sample size of 128 participants in both the intervention and control group.

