### Trial status

Enrolment into the study will start on September 1, 2021. We plan to complete the recruitment and data collection at baseline by September 2022, with a 12 months follow-up period on falls incidence and incidence of fall-related injuries until September 2023. This study has been registered with the Netherlands Trial Register on 13 February 2021 (NL9248).

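### The protocol contradicts itself on whether fall-related injuries are a primary outcome; the trial is sized for the number of falls only, at one alpha of 0.05

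*Protocol article*

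**What the plan says.** The sections of the protocol article fall into two groups.

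Injuries treated as primary, or at least as not secondary:
- Abstract, Methods paragraph: "Primary outcomes are the number of falls and fall-related injuries over 12 months follow-up". The noun is plural, and the list of secondary outcomes that follows does not include injuries.
- Secondary outcome measures, opening sentence: "Besides the number of falls and fall-related injuries, positive effects on physical functioning" and other measures are assessed. Injuries stand with falls, outside the secondary set.
- Discussion, paragraph on additional strengths: falls and fall-related injuries are placed on one side and multiple secondary outcomes on the other. The same paragraph says the study is not powered for the secondary measures.

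One primary outcome, all falls:
- Primary outcome measure: "The primary outcome in this study is the number of falls, with or without injuries".
- Statistical analysis, opening paragraph: the primary outcome is again singular, in the sentence on reporting missing data.
- Sample size: the target is worded as "To obtain a reduction of 50% in the number of falls between the intervention and control group". The section asks for 106 per group, with power 0.80 and one alpha, 0.05. No injury rate, injury effect or second alpha appears.

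Two places are neutral. The aim at the end of the Background ("on the number of falls with and without injuries for community-dwelling adults of 65 years or older with an increased fall risk") fits the Methods definition. Trial status ("with a 12 months follow-up period on falls incidence and incidence of fall-related injuries") names both outcomes without ranking them. No section shown lists injuries as secondary; the image of Table 2 is not available, so nothing is inferred from it.

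**The concern.** Which outcome is primary decides what the trial may claim, and that choice belongs to the protocol. An analysis plan can implement it, but here any plan would have to depart from either the abstract or the Methods.

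Two things are at stake. First, if falls and injurious falls give different answers, the published text lets a reader treat either one as a primary result, and the choice could be made after the data are known. Second, a reader of the Discussion would take injuries to be outside the measures for which power is disclaimed, and so to be powered. The Sample size section does not support that. Injurious falls are a subset of all falls, so for the same relative reduction they carry less information.

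**Working it through.** **The plan's own figure.** The Sample size section gives 106 per group for a 50% reduction, power 0.80 and alpha 0.05, with no control rate or dispersion, so 106 cannot be reproduced from its own inputs. It can be approached by assumption. The Background says more than one-third of older adults fall at least once a year. Comparing proportions 1/3 and 1/6 (two-sided 0.05, power 0.80, pooled-variance formula) gives 105 per group; 0.33 against 0.165 gives 107. Either way the sizing concerns falls. Sidedness is not stated; two-sided is assumed throughout. Power 0.80 is taken as operative, since the printed beta of 0.02 does not agree with it.

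**Error rate under each reading.**
1. Falls the only primary (Methods): 0.05.
2. Both primary, both must succeed: no inflation; power is limited by the injury comparison.
3. Both primary, each tested at 0.05, either suffices: above 0.05, by an amount that depends on the correlation r of the two tests.

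For reading 3, assume a negative binomial fall count with mean mu per year and dispersion k, each fall being injurious with probability q. Then

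r = sqrt[ q(1 + k·mu) / (1 + k·q·mu) ]

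- mu 0.7, k 1, q 0.3: sqrt(0.3 × 1.7 / 1.21) = 0.65. Bivariate normal family-wise error: 0.086.
- mu 1.2, k 2, q 0.5: sqrt(0.5 × 3.4 / 2.2) = 0.88. Family-wise error: 0.072.

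The range is therefore about 7 to 9%.

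**Power for injurious falls at 106 per group**, for a 50% reduction. None of mu, k or q is in the document. Wald test on the log rate ratio:

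var = (1/m + 1/(0.5m) + 2k) / 106, with m = mu for all falls and m = q·mu for injurious falls; power = Phi( ln 2 / sqrt(var) − 1.96 )

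| mu, k | All falls | q = 0.5 | q = 0.3 |
|---|---|---|---|
| 0.7, 1 | 0.81 | 0.59 | 0.42 |
| 0.8, 1 | 0.85 | 0.64 | 0.47 |
| 1.2, 2 | 0.80 | 0.66 | 0.53 |

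Worked row (0.8, 1, q = 0.5): m = 0.4, var = (2.5 + 5 + 2)/106 = 0.0896, square root 0.299, ln 2/0.299 = 2.315, power = Phi(0.355) = 0.64.

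These pairs were chosen because they give all falls about 80 to 85% power, in line with the plan. Other pairs in the same box give 0.39 (0.7, 2, q = 0.3) to 0.77 (1.2, 1, q = 0.5).

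A cruder method starts from exactly 80% power for falls and takes information as proportional to events: power = Phi(2.80 × sqrt(q) − 1.96). This gives 0.51 at q = 0.5 and 0.34 at q = 0.3. It also gives 0.14 at q = 0.1.

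**If alpha were split.** At 0.025 each, power for falls at 106 per group is Phi(2.80 − 2.24) = 0.71. Restoring 0.80 multiplies n by 1.211: 106 × 1.211 = 128.4, so 129 per group before dropout.

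**The case against.** The strongest reply is that the body of the article governs. The Methods and the Sample size section agree on one outcome and one alpha, and on that reading the error rate is 5% and the sizing fits. The abstract could be loose shorthand for falls with or without injury. The Secondary outcome measures section never calls injuries primary. Any multiplicity rule may sit in an analysis plan that is not shown.

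Much of this stands. A reader might infer that the trial gives itself two chances at 0.05. The document does not support that: it would require both that the abstract override the Methods and that success on either outcome be enough, and neither is stated. The absence of an alpha split is not a fault of this article. A reader might also quote 1 − 0.95² = 9.75% as the error rate, but that needs independent tests, and injurious falls are contained in all falls. The power figures rest wholly on assumed rates, dispersion and injury share; what the document itself shows is that injuries have no stated sizing. The aim in the Background needs no correction, and nothing can be said about the registry entry, which is not at hand.

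The contradiction survives. The abstract's plural does not read as one combined outcome, its secondary list omits injuries, and two further sections place injuries outside the secondary set. It is more than one stray phrase.

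**Conclusion.** The point holds as an inconsistency in the definition of the primary outcome. The abstract makes fall-related injuries primary, and the Secondary outcome measures section and the Discussion lean the same way. The Primary outcome measure and Sample size sections support a single primary, the number of falls, at one alpha of 0.05.

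The statistical consequence is conditional. With falls alone as primary there is no inflation and no change in sample size. Only if both outcomes were primary and either sufficed would the family-wise error rise to about 7 to 9%. In that case injuries would also hold primary status with power of roughly 40 to 65% for a 50% reduction, or 34 to 51% by the cruder method. All these figures assume 0.7 to 1.2 falls per year, dispersion 1 to 2 and 30 to 50% of falls injurious.

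It should be settled before outcome data are seen, because it fixes what counts as success and costs little to correct.

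**What to change.** State the same thing in the abstract, Primary outcome measure, Secondary outcome measures and Discussion: the single primary outcome is the number of falls over 12 months, tested at 0.05, as the Methods and Sample size sections already have it. Name the number of injurious falls as a key secondary outcome, for example tested only after a significant primary result and otherwise reported as an estimate with confidence interval. Other hierarchies would serve if written down.

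The cost is wording. The sample size is unchanged, and injuries lose the primary status that the abstract gives them.

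If the sponsor wants injuries as co-primary, the protocol must state the success rule (either or both) and the alpha for each, and restate the power with an assumed injury rate. With alpha halved, holding 80% for falls alone needs 129 per group before dropout. With the plan's own 20% add-on that is 129 × 1.2 = 154.8, so 155 per group and 310 in total, against 256 now. With division by 0.8 it is 161.25, so 162 per group and 324 in total. Neither total would by itself secure power for injuries.

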#### Primary and secondary outcomes

The effectiveness of the In Balance intervention in comparison with a control group will be analysed with multilevel mixed model regression analyses for both primary and secondary outcomes. Three hierarchical levels will be included in the mixed models; therapist, participant and time. If necessary, analyses will be adjusted for confounders and stratified for the presence of potential effect modifiers. The primary effect in these analyses is described by the coefficient of the time treatment interaction term. To identify possible differences in intervention effects between non-frail and pre-frail respondents, an a priori subgroup analysis will be performed, stratified for frailty level (non- and pre-frail).

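### The abstract and aim describe the primary analysis as stratified by frailty, but the Methods make frailty a subgroup analysis and the sample size covers only the whole-sample comparison

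*Protocol article*

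**What the plan says.** Four places in the protocol article bear on which comparison is primary.

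- **Abstract, Methods:** "Mixed model analyses will be conducted for both primary and secondary outcomes and will be stratified for non-frail and pre-frail adults". No whole-sample analysis is named.
- **Background, closing aim:** effectiveness and cost-effectiveness are to be assessed in older adults "with an increased fall risk, stratified for frailty status (non-frail and pre-frail").
- **Statistical analysis, Primary and secondary outcomes:** the primary effect is a single coefficient, the time-by-treatment interaction, with no stratum attached. Frailty then enters separately, to look for differences in effect: "an a priori subgroup analysis will be performed, stratified for frailty level (non- and pre-frail").
- **Sample size:** the target is a halving of falls in one comparison of the two randomised groups, and for this "a minimum of 106 persons are required per group". After dropout the total is 256. There is no calculation for either frailty stratum.

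Two further places give context. The section on recruitment and randomization stratifies randomization by frailty and aims for 30-50% pre-frail and 50-70% non-frail participants. The Discussion lists stratification by frailty among the strengths of the study.

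**The concern.** Read literally, the abstract and the aim give two stratum-level results for each primary outcome. The analysis and sample size sections give one result for everyone randomised. These are different comparisons with different precision, and the same data can be significant on one and not on the other. A reader of the abstract would take the stated 80% power to belong to the stratified analysis, whereas it belongs to the whole sample.

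The Discussion warns that the study is not powered for the secondary outcomes but gives no such warning for the frailty strata. A finding in one stratum that disagrees with the overall result is foreseeable, and the text points both ways on which of them answers the aim.

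**Working it through.** **1. The plan's own figures**

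The sample size section states "Taking into account a dropout rate of 20%, the total required sample size is 256 participants". Multiplying by one plus the dropout rate gives 106 × 1.2 = 127.2, rounded up to 128 per group and 256 in total, so the stated total is reproduced. (Dividing by 0.8 would give 133 per group; that is a separate matter.)

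The section gives no control rate. Taking 33% fallers per year as an assumption (the Background says more than one-third), halved to 16.5%, with two-sided alpha 0.05 and power 0.80:

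n = [1.96 × √(2 × 0.2475 × 0.7525) + 0.842 × √(0.33 × 0.67 + 0.165 × 0.835)]² / 0.165² = 106.2

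This is in line with 106 per group for one whole-sample comparison. The section also prints a beta of 0.02, which does not match power 0.80. At power 0.98 the same assumptions need 217 per group, so 0.80 is used below. The beta figure is a separate defect.

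**2. Power if the strata are the primary analysis**

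Assumptions: the whole-sample test has exactly 80% power, the effect is the same in both strata, information is proportional to stratum size, and tests are two-sided at 0.05 (the article does not state sidedness).

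The expected whole-sample z-statistic is 1.960 + 0.842 = 2.802. A stratum holding share f of the sample has expected z of 2.802 × √f, so its power is Φ(2.802√f − 1.960). The strata are independent, so the chance that both are significant is the product of the two powers. When both are significant in the direction of benefit, the whole-sample test is significant too. The chance that the whole-sample test is significant but at least one stratum is not is therefore 0.80 minus that product.

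| Pre-frail share | Pre-frail per group (of 106) | Power, pre-frail | Power, non-frail | Both strata significant | Overall significant, not both strata |
|---|---|---|---|---|---|
| 30% | about 32 | 0.335 | 0.650 | 0.218 | 0.582 |
| 40% | about 42 | 0.425 | 0.583 | 0.248 | 0.552 |
| 50% | 53 | 0.508 | 0.508 | 0.258 | 0.542 |

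**3. Conditional worst case for the error rate**

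Suppose all three contrasts (overall, pre-frail, non-frail) were confirmatory at two-sided 0.05 without adjustment, with no effect in either stratum. With Z_pre and Z_non independent standard normal and Z_all = √f·Z_pre + √(1−f)·Z_non, the chance that at least one exceeds 1.96 in absolute value, by numerical integration, is:

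- f = 0.30: 11.37%
- f = 0.40: 11.47%
- f = 0.50: 11.50%

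Simulation with 4 million draws agrees. For a false claim of benefit only (upper tail 0.025 each) the figure is 5.7-5.8% against a nominal 2.5%. With the two strata alone it is 1 − 0.95² = 9.75% in either direction. With the whole-sample contrast as the sole primary test it is 5%.

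**The case against.** The strongest reply is that the Methods already settle the matter. They name one primary coefficient, give the frailty split the role of a subgroup analysis meant to look for differences in effect, and the sample size agrees. On that view the phrases in the abstract and aim are shorthand for the same subgroup analysis, and neither says that the whole-sample comparison is dropped. The power figures would hold for any trial with subgroups of these sizes.

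Much of this stands. A reader might infer that the overall, pre-frail and non-frail results can each decide effectiveness at 0.05, so that the trial's false-positive rate is about 11%. The article does not support that. It nowhere says that a stratum result alone establishes effectiveness or that all three contrasts are confirmatory, and alpha 0.05 appears only in the sample size section, for one comparison. Detailed multiplicity rules may sit in an analysis plan that is not shown, so their absence here is no finding. The 11% figure also counts significant results in the direction of harm. Nor does the Discussion make the strata confirmatory: it speaks of investigating impact in different groups.

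What the reply does not remove is the printed mismatch. The abstract says outright that the primary-outcome models will be stratified, and the aim carries the same qualifier. An analysis plan that chose either reading would still conflict with one part of the published text.

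**Conclusion.** The point holds as an inconsistency in wording with a real consequence for power. The Methods and the sample size fit a single whole-sample primary comparison; the abstract and the aim describe a stratified one. If the latter are followed, the trial does not have its stated 80% power for what it reports as primary: about 34-51% in the pre-frail and 51-65% in the non-frail, with both strata significant in 22-26% of trials. In 54-58% of trials the whole-sample test would be significant while at least one stratum was not. These figures rest on exactly 80% overall power, equal effects, the planned 30-50% pre-frail share and two-sided 0.05 tests. The error rate of 11.4-11.5% is only a conditional worst case under a rule that the article does not state; it is not the plan's error rate.

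**What to change.** Align the abstract, the aim at the end of the Background, and the section on primary and secondary outcomes. State in each that the single primary test is intervention versus control in all randomised participants, at two-sided alpha 0.05, with frailty stratum (the randomisation factor) as a covariate. In the abstract and aim, replace the wording that the analysis is stratified with wording that subgroup estimates will be given for non-frail and pre-frail adults. Report those as supportive estimates with 95% confidence intervals that do not by themselves establish effectiveness.

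This matches the existing sample size and needs no new data or participants. It should be settled before group assignment is unblinded. The small downside is that the trial can then make no confirmatory claim for one frailty group alone.

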**Discussion:**

This trial will provide insight into the clinical and societal impact of an implemented Dutch fall prevention intervention and will have major benefits for older adults, society and health insurance companies. In addition, results of this study will inform healthcare professionals and policy makers about timely and (cost-)effective prevention of falls in older adults.

**Trial registration:**

Netherlands Trial Register: NL9248 (registered February 13, 2021).

## Background

Falls are a major cause of mortality and morbidity in older adults [1]. More than one-third of community-dwelling adults aged 65 years or older falls at least once per year [2]. The number of falls is expected to increase even further due to the ageing of the population [3–5]. Falls in older adults often result in injury with 109,000 older adults visiting an Emergency Department due to a fall-related injury in the Netherlands in 2019 [6]. Besides the risk of injuries, falls may also increase fear of falling [7]. Fear of falling may result in a reduction in physical activity in daily life, which can lead to a decreased muscle strength and an increased fall risk [8–11]. Falls and its sequelae can lead to a decreased quality of life up to 9 months after a fall, suggesting that even after that amount of time older adults are still suffering from their fall and its consequences [12, 13]. Fall-related injuries result in considerable healthcare costs, which are estimated at more than 1 billion euros in the Netherlands [6]. On top of these healthcare costs, other costs also have to be taken into account, such as individual expenses, help from family and/or friends and productivity losses due to absence from work or unpaid activities [14–16]. The alarming impact of falls on older individuals, healthcare and our greying society renders the prevention of falls and fall-related injuries highly urgent [17, 18].

Systematic reviews have shown fall prevention programmes to be effective in reducing the risk of falls among older adults [19, 20]. Group interventions appear more effective than individual programmes, because of higher compliance of participants in the group intervention [21, 22]. Despite the evidence that falls can be prevented by fall prevention programmes, barriers for practical implementation may harm the impact of these programmes. It can for example be questioned whether effectiveness maintains after adjustments in the intervention when implemented, which indicates the importance of re-evaluating implemented interventions [18–20].

An effective group fall prevention intervention, that is widely implemented in the Netherlands, is the In Balance intervention. In Balance is a relatively inexpensive fourteen-week group intervention that requires minimal equipment and aims to reduce falls by increasing awareness, balance and strength in older adults at risk of falling [23]. The first four weeks of In Balance include counselling and education meetings once per week on topics regarding fall prevention to increase knowledge about preventing falls, and to increase awareness of fall risk and balance disruption. The last ten weeks comprise two one-hour exercise sessions per week. Exercises are derived from principles of Tai Chi and are mainly focused on physical balance and strength.

In 2006, Faber and colleagues demonstrated that the 20-week In Balance intervention resulted in a fall-risk reduction of 61% in pre-frail older adults, compared to usual care in a residential care setting, whereas in frail older adults the risk of becoming a faller increased considerably [24]. This difference in effect may be because frail participants were not able to perform the exercises as effectively as the pre-frail group [25]. Based on the positive findings in the pre-frail group, the In Balance fall prevention programme has been widely implemented in the Netherlands by certified therapists. After implementation, the target group was extended to a group mainly consisting of independently living older adults. Moreover, the duration of the intervention was shortened from twenty to fourteen weeks, for practical reasons and adherence, based on indications that the largest physical improvements in the study by Faber and colleagues were seen in this initial period [24].

Considering the adjustments in both duration and target population of the original In Balance intervention, re-evaluation of the effectiveness of the intervention is urgently needed. Moreover, evidence on the cost-effectiveness of fall prevention programmes is scarce [26]. Cost-effectiveness analysis of the In Balance intervention would allow insurance companies, policy- and decision makers to allocate health resources efficiently. Therefore, this study aims to assess the effectiveness and cost-effectiveness from a societal perspective of the In Balance fall prevention intervention compared to written general physical activity recommendations on the number of falls with and without injuries for community-dwelling adults of 65 years or older with an increased fall risk, stratified for frailty status (non-frail and pre-frail).

